### Sample size

The sample size calculation is based on the primary outcome. It is assumed that the control group experience an average of two exacerbations, and the intervention group experienced one exacerbation during the trial period from baseline to the 6-months follow-up. With a power of 90%, a variance of two exacerbations for both groups, a two-sided significance level of 0.05, the required sample size is estimated to be at least 85 participants in each group [62]. Based on experience from the original large-scale trial, TeleCare North [34], a loss to follow-up of 15% in each group is expected. Therefore, the total required sample size in each arm is the estimated to be approximately 100 participants.

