## Introduction

### Background

Chronic obstructive pulmonary disease (COPD) imposes a substantial economic and social burden globally [1, 2]. The global prevalence was estimated to 251 million cases in 2016 [3]. COPD is the third leading cause of morbidity and mortality worldwide [4] and is responsible for 3 million deaths annually [5]. The disease is projected to increase further over the coming decades with an estimated mortality of 4.5 million deaths annually by 2030 [6] and 5.4 million deaths annually by 2060 [2].

According to Global Initiative for Chronic Obstructive Lung Disease (GOLD) COPD refers to a group of progressive lung diseases characterized by not fully reversible airflow limitation that causes long-term breathing problems [2, 7]. In mild stages of COPD, the symptoms are present only by infections or by strenuous physical exertion. In the more severe stages of COPD, the symptoms are more prominent and will usually increase over time [8, 9]. Most patients with COPD experience periods where their symptoms vary from day to day [2]. However, sometimes patients also experience acute worsening of their usual symptoms, which are referred to as exacerbations. According to GOLD, an exacerbation is defined as “an acute worsening of respiratory symptoms that results in additional therapy” [7]. The frequency of exacerbations increases with the severity of COPD [10] and exacerbations contribute to the worsening of COPD at a long-term level [8, 11, 12]. Moreover, exacerbations are associated with increased mortality as well as impaired prognosis, decline in lung function, worsen cardiovascular comorbidities, and decreased health-related quality of life [8, 12, 13]. More than four out of five exacerbations can be managed outside the hospital with proper medication, whereas more severe exacerbations require ventilator support and hospitalization [7]. Early treatment is associated with faster recovery and decreased risk of emergency hospitalization [14]. However, patients with COPD often delay or fail to seek treatment during exacerbation [15], and it has been estimated that 40% to 70% of exacerbations remain unreported to healthcare personnel [14–16]. This highlights the importance of detecting exacerbations earlier in order to facilitate early and preventive treatment [14, 17].

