### Statistical methods

Overall, the statistical methods will follow an intention-to-treat principle [54]. Results from the trial will be presented in accordance with the Consolidated Standards of Reporting Trials (CONSORT) for randomized trial guidelines [55] as well as the Consolidated Health Economic Evaluation Reporting Standards (CHEERS) [56]. Missing data will be subject to multiple imputation [57]. If there is a need for an adjustment of the participants’ baseline characteristics due to differences among the two groups, this will be performed.

To assess the primary outcome, Poisson regression with exponentiated coefficients will be used to produce incidence rate ratios. In assessing HRQoL, generalized linear models [58] will be used to model EQ-5D-5L and the two SF12v2 summary scores; the physical component score (PCS-12) and the mental component score (MCS-12). To assess the secondary outcome of cost-effectiveness, an ICER point estimate will be calculated after 6 months follow-up. The ICER is defined as the difference in the average costs between the two alternatives divided by the difference in average effectiveness between the same alternatives [59]. For the ICER calculation, the effectiveness for both alternatives is assessed based on the utility scores from the EQ-5D-5L questionnaire, with Danish societal weights that are unpublished but under journal peer review [50]. With the help of information on within-trial survival time, QALYs can then be elucidated with linear interpolation of utility scores between baseline and follow-up at six months as the area under this curve [59].

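### The stated variance of 2 gives 43 participants per arm, not 85; the printed figures reproduce only with a standard deviation of 2, and the power of the planned rate-ratio analysis depends on which was meant

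*Protocol article*

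**What the plan says.** The Sample size section bases the calculation on the primary outcome. For the control arm, "It is assumed that the control group experience an average of two exacerbations"; for the other arm, "the intervention group experienced one exacerbation during the trial period", over six months. The remaining inputs are "With a power of 90%, a variance of two exacerbations for both groups, a two-sided significance level of 0.05". The result is that "the required sample size is estimated to be at least 85 participants in each group". A 15% loss to follow-up then raises this to about 100 per arm. Allocation is 1:1 (Study design).

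For the analysis of the same outcome, the Statistical methods section says that "Poisson regression with exponentiated coefficients will be used to produce incidence rate ratios". The Primary outcome section defines the counted exacerbation as an acute hospitalisation from any cause.

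**The concern.** Every input of a two-means calculation is printed, so the result can be checked directly. It comes out at about half the stated figure. A factor of two in the sample size is what results when a value entered as a standard deviation of 2 is reported as a variance of 2, or the reverse.

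The word matters beyond the arithmetic. A variance of 2 with a control mean of 2 looks like Poisson data. A variance of 4 does not, and Poisson regression is the named analysis. Moreover, the calculation concerns a difference in means while the analysis estimates a ratio of rates, so the power quoted for the first does not carry over to the second. A reader who later weighs a null result, or a shortfall in recruitment, against the 90% figure could not tell what that figure refers to.

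**Working it through.** **Inputs** (Sample size, unless noted): means 2 and 1, so difference 1 and rate ratio 0.5; variance 2 in both arms; power 90%; two-sided α 0.05; 1:1 allocation (Study design); loss 15%.

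**1. The plan's own figure.** n per arm = 2σ²(1.960 + 1.2816)²/δ², with (1.960 + 1.2816)² = 10.507 and δ = 1.

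- Variance 2 as written: 2 × 2 × 10.507 = 42.03, so 43 per arm. After 15% loss, 43/0.85 = 50.6, so 51.
- SD 2 (variance 4): 2 × 4 × 10.507 = 84.06, so 85 per arm. After loss, 85/0.85 = 100.

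Solving the t-test version instead gives 43.01 and 85.03. Only SD 2 leads to both printed figures, 85 and 100.

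**2. Other routes to 85 per arm.** None was found:

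| Method | n per arm |
|---|---|
| One-sided two-means, variance 2 / SD 2 | 35 / 69 |
| Poisson log rate ratio | 33 |
| Poisson rate difference | 32 |
| Poisson log rate ratio, overdispersion 2 | 66 |
| Negative binomial, dispersion 0.5 / 1 / 2 | 55 / 77 / 121 |
| Log rate ratio, delta method, variance 2 / 4 | 55 / 110 |

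**3. Power of 85 per arm for a difference in means.** Φ(δ/√(2σ²/n) − 1.96):

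- Variance 2: Φ(1/√(4/85) − 1.96) = 99.6%.
- SD 2: Φ(1/√(8/85) − 1.96) = 90.3%.

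**4. Power of 85 per arm for the rate ratio.** By the delta method, Var(log RR) = (v₁/m₁² + v₂/m₂²)/n, and log 2 = 0.6931.

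- Variance 2 in both arms: (2/4 + 2/1)/85 = 2.5/85; Φ(0.6931/√(2.5/85) − 1.96) = 98.1%.
- Variance 4 in both arms: (4/4 + 4/1)/85 = 5/85; Φ(0.6931/√(5/85) − 1.96) = 81.5%. For 90%, n = 10.507 × 5/0.4805 = 109.3, so 110 per arm.
- Variances 4 and 2, that is, variance proportional to the mean: (4/4 + 2/1)/85 = 3/85; Φ(0.6931/√(3/85) − 1.96) = 95.8%.

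**5. What SD 2 implies for Poisson regression.** The variance-to-mean ratios are 4/2 = 2 (control) and 4/1 = 4 (intervention), whereas the Poisson model assumes 1. If both means are 2 and both variances 4, the true standard error is √2 times the model's, so the type I error is 2[1 − Φ(1.96/√2)] = 16.6%; simulation gave 16.3%.

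Results with negative binomial counts, means 2 and 1, variance 4, 85 per arm:

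| Test of the rate ratio | Formula | Simulation |
|---|---|---|
| Robust standard error | 81.5% | 84.6% |
| Quasi-Poisson | 84.1% | 86.0% |
| Negative binomial regression | – | 89.4% (1,500 trials) |
| Uncorrected Poisson | 96.3% | 97.8% |

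The last row is not usable power, because that test does not hold its 5% level.

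**The case against.** The strongest reply is that the trial is no worse off. Taken literally, variance 2 with 85 per arm exceeds 90% power for the means (99.6%) and for the rate ratio (98.1%). This stands: the direction of the error is unknown, and the article does not show that the trial is underpowered.

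A reader might infer that the planned analysis has only 82–84% power. The documents do not support that. The analysis they name is Poisson regression, and the article mentions no correction of its standard error. Under SD 2 the uncorrected version rejects in about 98% of simulated trials, and its fault is a false-positive rate near 16%. The figure of 82–86% needs SD 2, variance 4 in both arms and a robust or quasi-Poisson standard error together.

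A reader might also infer that the assumed control rate is too high, because the Background says: "More than four out of five exacerbations can be managed outside the hospital with proper medication". That sentence concerns exacerbations in the general clinical sense. The trial counts acute admissions from any cause and states that the calculation rests on that outcome, so one fifth cannot be applied to the assumed mean. Nor is the lack of a source for that mean a finding, since a condensed article may leave it to the full protocol.

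Finally, 85 could be a two-arm total at variance 2, since 2 × 42.03 = 84.06. The text says that the figure applies to each group and raises it to about 100 per arm, so this reading is unlikely. It is one reason why SD 2 should be confirmed and not assumed.

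**Conclusion.** The sample size statement is wrong as written. Its inputs require 43 per arm, and it states 85. That SD 2 was used is very probable, since it alone gives both 85 and 100, but it is an inference.

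The consequence for the primary analysis is conditional. With variance 2, rate-ratio power at 85 per arm is about 98%. With SD 2 in both arms, it is about 82–86% with a robust or quasi-Poisson standard error and about 89% with negative binomial regression. It is about 96% if the variances are 4 and 2. Under SD 2, Poisson regression without a correction would not hold its 5% level. All these figures take the assumed means of 2 and 1 as given, and the simulations assume negative binomial counts.

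**What to change.** State whether 2 is the variance or the standard deviation, and correct the sentence so that the printed inputs give 85. Then restate the power of 85 analysed per arm for the rate-ratio comparison that is planned. Give the dispersion assumed in each arm, and name a standard error or model that allows for overdispersion.

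This costs a corrected sentence and a short restatement of power. Enrolment stays at about 200. If SD 2 is confirmed for both arms, the quoted power may fall somewhat below 90%, and it is better to say so before the results are known.

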## Discussion

In this prospective, parallel, two-armed randomized controlled trial, a COPD prediction algorithm will be tested in a telehealth system with an aim to predict exacerbations in a timely manner. The COPD prediction algorithm is embedded into the general offer of telehealth to patients with COPD in the North Denmark Region. The COPD prediction algorithm will be used to support specialized COPD community nurses in their clinical decisions by alerting them regarding any deviations from the participants’ expected physiological parameters, which may indicate potential exacerbations. The COPD prediction algorithm is expected to improve the telehealth intervention, because the algorithm will use time-series data obtained through weekly repeated average measurements of physiological parameters. In addition, the frequency of the specialized COPD community nurses’ monitoring will be enhanced, as the specialized COPD community nurses not only assess data once a week, but are notified if the COPD prediction algorithm alarm is activated.

An expected strength of the present trial is the pragmatic design with minimal interference into usual practice. To our knowledge, this is the first Danish trial that tests a COPD prediction algorithm into a current operational telehealth system. Another strength is that the trial duration includes a mix of seasons, i.e., autumn and winter, which may increase the generalizability of the results as most exacerbations always occur in winter.

The calculated sample size might be difficult to achieve. A large sample size is desirable to power the trial and to enhance the generalizability of the results. To ensure adequate participant enrollment, the specialized COPD nurses will contact all potential participants in their area. Moreover, the inclusion criteria for the trial are relatively open to ensure a sufficient pool of potential participants. The COPD prediction algorithm performance is highly dependent on the two additional oxygen saturation measurements that the participants have to perform weekly. Thus, a potential risk for the results of the trial is that the participants fail to perform the extra measurements. In addition, the performance of the COPD prediction algorithm highly depends on the specialized COPD community nurses' involvement in assessing measurements, when a COPD prediction algorithm alarm is activated. Therefore, the trial seeks to enhance the involvement of the nurses by repeated training and meetings prior to the trial.

Once the trial has been completed, the results will be published in peer-reviewed journals. The results will also be presented for relevant partners, such as the specialized COPD community nurses and the TeleCare North administration office. The trial has the potential to improve the telehealth intervention in patients with COPD in the form of more intelligent, decision-based monitoring. In the future, it could be relevant to test and implement a similar prediction algorithm among other disease groups, as telehealth becomes more relevant for various diseases and patients with multiple comorbidities.

## Dissemination plans

The results of the trial will be published in international scientific journals. All results are reported in anonymized form. Results will be published regardless of whether or not they are accepted by international journals, and whether results are positive, negative, or inconclusive. Authorship will be granted to those who have contributed to the design, conduct, interpretation, and reporting of the trial.

## Data Availability

All data will be stored in REDCap (Research Electronic Data Capture). Only researchers from Aalborg University will have access to the trial dataset.
